#### Group B (Placebo FES‐Integrated UPT)

2.7.2

This group will receive 30 min of placebo FES combined with 30 min of UPT, three times weekly for 8 weeks, identical to Group A in treatment duration and therapist interaction. For placebo FES, electrodes will be positioned identically to those in the active FES group over the wrist extensor muscles; however, the stimulation intensity will be set below the motor threshold and gradually reduced after a brief initial sensory stimulation period, thereby preventing visible muscle contraction. This approach is intended to maintain participant blinding and enhance placebo credibility while avoiding therapeutic neuromuscular effects. Each participant will receive a total of 24 treatment sessions [18].

To ensure intervention fidelity and minimize performance bias, all physiotherapists involved in treatment delivery will complete training sessions before participant enrollment. A detailed intervention with describing electrode placement, stimulation parameters, task progression, and UPT procedures will be used throughout the study. Treatment adherence will be monitored using structured session checklists completed after each session to ensure protocol compliance and consistency across therapists and participants.

### Outcome Measurements

2.8

The primary outcome measures will focus on hand pain and function, with hand pain measured using the Numeric Pain Rating Scale (NPRS) and hand function using the Fugl‐Meyer Assessment for Upper Extremity (FMA‐UE). Secondary outcomes will include muscle tone and manual dexterity, with muscle tone measured using the MAS and manual dexterity using the Box and Block Test (BBT). Spasticity will specifically be evaluated in the wrist flexors, finger flexors, and elbow flexors of the affected limb, as these muscle groups are commonly associated with post‐stroke upper extremity spasticity patterns. Individual participant sociodemographic information related to stroke will also be collected at baseline assessment. The primary and secondary outcomes will be measured at four time points: baseline, mid‐intervention (week 4), post‐intervention (week 8), and 12‐week follow‐up (week 20).

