Pain after stroke can impair psychological well‐being, daily function, working abilities, and a person's quality of life [12, 13, 14]. The prevalence of post‐stroke pain ranges from 19% to 74%, influenced by pain classification systems, follow‐up duration, and assessment methods. Central pain can result from thalamic lesions, while peripheral pain can result from secondary deficits and abnormal muscle tone [15]. After a stroke, the upper extremities are the most commonly affected site of peripheral pain. However, hand pain is reported in 4.6% of the elderly stroke population [16, 17, 18]. Functional status of the upper extremity is a significant focus during rehabilitation for people with a stroke [19]. Over the last 10 years, the number of studies focusing on stroke rehabilitation of the upper extremity has increased rapidly [18]. Numerous studies have evaluated the effectiveness of physiotherapy interventions for stroke by comparing experimental treatments with standard or conventional therapy [18, 19, 20, 21]. A variety of therapeutic approaches have been used to improve upper‐extremity motor function following a stroke, including Functional Electrical Stimulation (FES) [9, 10, 18, 19, 20]. FES involves the use of electrical impulses that stimulate the nerves attached to paralysed muscles. It can be employed as an intervention during upper extremity rehabilitation because it stimulates the contraction of paralysed and weak muscles, enabling a person to perform movements and actions such as gripping a key, holding a toothbrush, and using utensils [20]. FES can be used to create movements or functions that resemble typical voluntary movements for the purposes for which those movements are intended [21, 22].

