### Sample Size Calculation

2.3

Sample size calculation is performed using G*Power software version 3.1.9.7 for a two‐tailed independent‐groups test comparing two group means. The effect size (Cohen's *d*) is set to 0.5 (medium effect) based on prior research in post‐stroke rehabilitation [23]. The α value is predetermined as 0.05, and the power (1–β) is 0.80 to limit the risk of Type II error. Based on these parameters, we will need 64 individuals per group, for a total of 128 participants. Finally, we plan to recruit 140 participants (70 per group), allowing for an anticipated dropout rate of approximately 10%.

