#### Inclusion Criteria

2.6.1

Participants must meet all of the following to be eligible for the study: (1) Confirm diagnosis of unilateral ischemic stroke verified by CT or magnetic resonance imaging (MRI) by a neurologist [24]; (2) Age between 40 and 70 years; (3) Stable vital signs with normal levels of consciousness; (4) Brunnstrom recovery stage between 3 or less for the affected upper extremity function [25, 26]; (5) Presence of mild‐to‐moderate spasticity in the affected upper extremity, based on Modified Ashworth Scale (MAS) score of 1 to 2 in the wrist flexor muscles; (6) Stroke onset between 1 and 3 months before enrollment [27]; (7) Willingness and ability to provide informed consent to participate in the study.

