#### Exclusion Criteria

2.6.2

Participants will be excluded if they: (1) Have a previous history of stroke, including reversible ischemic or hemorrhagic stroke; (2) Exhibit severe cognitive impairments or significant speech and communication difficulties; (3) Have a diagnosis of any mental health disorders (e.g., schizophrenia); (4) Have an implanted cardiac pacemaker [28].

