#### Numeric Pain Rating Scale (NPRS)

2.9.1

The NPRS will be used to measure hand pain. It is a reliable and valid 11‐point scale (0–10) measuring pain intensity, where 0 indicates no pain and 10 represents the worst imaginable pain. It is commonly used in healthy adults and patients with various pain conditions, including stroke. The NPRS demonstrates excellent reliability for stroke pain assessment (Cronbach's alpha ≥ 0.95; reliability > 0.95). It is quick to administer (approximately 1 min) and can be completed verbally or graphically [31].

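### Hand pain (NPRS) is a primary outcome, but no entry criterion requires hand pain and no expected prevalence is stated, so the 80% power is unsupported for it

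*Protocol article*

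**What the plan says.** Section 2.8 names two primary outcomes, NPRS hand pain and FMA-UE: "The primary outcome measures will focus on hand pain and function, with hand pain measured using the Numeric Pain Rating Scale (NPRS"). Section 2.9.1 defines the scale as one "where 0 indicates no pain and 10 represents the worst imaginable pain".

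Section 2.6.1 opens its list with "Participants must meet all of the following to be eligible for the study". The seven items cover stroke type, age, stability, Brunnstrom stage, wrist-flexor MAS, time since onset and consent. The four exclusions in section 2.6.2 cover earlier stroke, cognition and communication, mental health and pacemakers. Neither list mentions pain.

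The Introduction gives two prevalence figures. One is specific to the hand: "hand pain is reported in 4.6% of the elderly stroke population". The other is for post-stroke pain in general: "The prevalence of post‐stroke pain ranges from 19% to 74" per cent.

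Section 2.3 has one power calculation, for a two-tailed comparison of two group means. Its effect size "is set to 0.5 (medium effect) based on prior research in post"-stroke rehabilitation is tied to no named outcome. It yields 64 per group at 80% power, with 140 to be recruited. Section 2.13 plans an intention-to-treat analysis.

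**The concern.** A participant who enters with an NPRS of 0 cannot improve on it. If many do, the group means are pulled towards 0 and the between-group difference is diluted. The standardised effect in the whole randomised group is then much smaller than the effect in those who have pain.

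The other treatment targets are secured at entry: spasticity must be present and motor recovery must be limited. Pain is not. Yet reducing hand pain is half of the primary objective, and the one effect size in section 2.3 is the only power support for either primary outcome. If few participants have hand pain, a null NPRS result could not be told apart from a floor effect, and readers would wrongly credit it with 80% power.

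**Working it through.** **Inputs from the protocol article.** d = 0.5, two-sided alpha 0.05, power 0.80, 64 per group evaluable, 140 recruited (2.3); NPRS 0 to 10 with 0 as no pain (2.9.1); hand pain 4.6% in elderly stroke patients and any post-stroke pain 19% to 74% (Introduction).

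**Step 1. The plan's own figure.** A two-sample t-test at d = 0.5 needs 63.8, so 64 per group, and has power 80.1% there. The sample-size arithmetic is correct. The question is whether it applies to NPRS.

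**Step 2. Expected number with pain at 4.6%.** 140 × 0.046 = 6.4 participants, about 3 per arm. The other 95.4% score 0.

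**Step 3. A ceiling on d that needs no assumed mean or SD.** Let a share p have hand pain, the rest score 0, and no new pain arise. The most favourable case is that every control with pain scores the same value m and every FES participant scores 0.
- Difference in means: p·m
- Variance: m²p(1−p) in controls, 0 in the FES arm
- Pooled SD: m·√(p(1−p)/2)
- d_max = √(2p/(1−p)), whatever m is; any spread among those with pain lowers it

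At p = 0.046, d_max = √(0.092/0.954) = 0.31. Power at 64 per arm is about 41%, and about 164 per arm would be needed for 80%. On change scores, if those with pain in the two arms moved by equal amounts in opposite directions, the bound would be 2√(p/(1−p)) = 0.44, still below 0.5.

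Setting d_max = 0.5 gives 2p/(1−p) = 0.25, so p = 0.25/2.25 = 11.1%. Below that prevalence d = 0.5 is out of reach under these conditions. Above it, it is not.

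**Step 4. Power over a range of prevalence.** Assumptions, none of them in the documents: NPRS mean 5 and SD 2 in controls with pain; the FES arm has mean 3 and SD 2 in those with pain (a 2-point benefit); all others score 0. In each arm the mean is p·μ and the variance is p(SD² + μ²) − (p·μ)².

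Example at p = 0.50: the control mean is 2.5 and variance 0.5 × 29 − 6.25 = 8.25. The FES mean is 1.5 and variance 0.5 × 13 − 2.25 = 4.25. Pooled SD = √6.25 = 2.5, so d = 1.0/2.5 = 0.40.

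| Share with hand pain | Number of 140 | d (2-point benefit) | Power, 64 per arm |
|---|---|---|---|
| 4.6% | 6 | 0.10 | 8% |
| 19% | 27 | 0.21 | 21% |
| 50% | 70 | 0.40 | 61% |
| 74% | 104 | 0.59 | 91% |

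On these inputs d = 0.5 needs about 64% of participants to have hand pain. The result also moves with the assumed benefit: at 50% prevalence, 2.5 points gives d = 0.51 and power of about 82%.

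**The case against.** The strongest reply is that 4.6% describes a different population. The trial enrols people aged 40 to 70, one to three months after stroke, with wrist-flexor spasticity. The Introduction itself links peripheral pain to abnormal muscle tone and names the upper extremity as its commonest site. The protocol never offers 4.6% as its expected rate. This stands: the prevalence in this sample is unknown and may well be higher. It does not supply the missing figure, because the 19% to 74% range is for any post-stroke pain, not hand pain.

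A reader might therefore infer too much, namely that d = 0.5 could not occur on NPRS, or that the pain question cannot be answered. The documents do not support that. The impossibility ends at about 11% prevalence, and the table shows ample power at 74%.

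Three further points have some force. The mean, SD and benefit in the table are assumptions. New-onset pain in controls up to week 20 could widen the difference, although the stated objective is reducing pain. And section 2.3 does not tie d = 0.5 to NPRS, though as the only effect size given it is the only support that NPRS has.

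The nonparametric fallback in section 2.13 does not help. In a simulation under the same assumptions (scores rounded and kept within 0 to 10), Mann–Whitney power was about 5% at 4.6% prevalence and about 37% at 50%.

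**Conclusion.** The concern holds in this form: power for the NPRS primary outcome is not established and could be very low, because nothing in the eligibility criteria secures hand pain and no expected prevalence is stated. If 4.6% applied, the ceiling would be d = 0.31 with power of about 41%, assuming complete abolition of pain by FES and no new pain in controls. On the illustrative inputs, power ranges from 8% to 91% depending on prevalence. FMA-UE is not affected, and the calculation of 64 per group is correct. The trial had not begun recruiting at the time of the article (2.16), so this can still be settled in advance.

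**What to change.** **Section 2.3.** State that the 80% power at d = 0.5 applies to FMA-UE, and that power for NPRS depends on the share with baseline hand pain. Show the range with its assumptions.

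**Section 2.13.** Include baseline NPRS, or baseline hand pain yes/no, in the NPRS model. Report the NPRS effect among participants with baseline NPRS of 1 or more, and report new-onset pain in the rest. Baseline NPRS is already measured, so this adds no visits or patients. It does change the analysis model, so it is slightly more than a wording edit.

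**Which outcome is primary** is the investigators' choice:
- *Preferred low-cost option:* FMA-UE as sole primary outcome, NPRS as key secondary. The price is that the pain claim becomes secondary and may rest on few patients (about 6 of 140 at 4.6%, 27 at 19%).
- *If pain is to stay primary:* require baseline hand pain at entry in section 2.6.1 and state the recruitment cost. At 4.6%, 140/0.046 is about 3,000 otherwise eligible patients to be screened at one site; the number falls in proportion as prevalence rises.

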### Primary Outcomes

2.9

#### Numeric Pain Rating Scale (NPRS)

2.9.1

The NPRS will be used to measure hand pain. It is a reliable and valid 11‐point scale (0–10) measuring pain intensity, where 0 indicates no pain and 10 represents the worst imaginable pain. It is commonly used in healthy adults and patients with various pain conditions, including stroke. The NPRS demonstrates excellent reliability for stroke pain assessment (Cronbach's alpha ≥ 0.95; reliability > 0.95). It is quick to administer (approximately 1 min) and can be completed verbally or graphically [31].

#### Fugl‐Meyer Assessment for Upper Extremity (FMA‐UE)

2.9.2

The FMA‐UE will be used to measure hand function. It is a widely used, reliable procedure for evaluating motor function in post‐stroke hemiplegia, with reliability and internal consistency values ≥ 0.95 [32]. For the upper extremity, the total value is 66. It uses a 3‐point scale (0–2) to assess motor function, with scores interpreted as follows: < 33: Severe, 33–55: Evident, 56–62: Moderate, 63‐65: Mild motor dysfunction [33].

### Secondary Outcomes

2.10

#### Modified Ashworth Scale (MAS)

2.10.1

The MAS will be used to measure muscle tone in the affected upper extremity. It is a valid method for measuring muscle tone, where passive joint movement is scored from 0 (no increase in tone) to 4 (rigidity). The MAS shows good inter‐ and intra‐rater reliability (ICC = 0.61–0.91), though the 1+ grade may present some classification challenges [34].

#### Box and Block Test (BBT)

2.10.2

The BBT will be used to assess manual dexterity and provide a clearer understanding of hand function. It is a valid test for measuring manual dexterity and hand‐eye coordination. Participants will transfer wooden blocks between compartments within 1 min, with the total number of blocks moved constituting the score. The BBT has excellent validity, reliability (ICC = 0.93–0.98), and sensitivity to changes in upper extremity function post‐stroke [35, 36].

### Study Procedure

2.11

After recruitment, participants will receive a participant information sheet, and written informed consent will be obtained. Medical screening and physical assessment will then be conducted by trained assessors under the supervision of a physiotherapist. Baseline socio‐demographic and clinical data will be collected by a blinded assessor. Allocation to intervention groups will be concealed using sealed envelopes. Interventions will be provided free of charge, with participants responsible only for transportation costs. After 4 weeks of intervention, participants will be assessed for mid‐intervention measurements. Post‐intervention, participants will return to the assessor for outcome evaluation and receive follow‐up instructions. Follow‐up assessments will be scheduled by phone for the final in‐person evaluation. All study procedures will strictly adhere to the protocol approved by the Ethics Committee. Any deviations required due to emergency situations or unforeseen circumstances will be undertaken only after obtaining prior approval from the Ethics Committee.

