### Randomization and Blinding Procedures

2.5

Following consent, participants will be randomly assigned in a 1:1 ratio to either Group A or Group B using simple randomization performed through Excel's = RAND() function by an independent research assistant not involved in recruitment, treatment, or assessment. Allocation concealment will be ensured using sequentially numbered, opaque, sealed envelopes prepared by an independent assistant. This study will employ participants, and outcome assessors will be blinded to group allocation throughout the study period. Due to the nature of the intervention, treating physiotherapists administering FES cannot be blinded; however, they will not participate in outcome assessment or data analysis. Participants in both groups will receive identical treatment durations, therapist interactions, electrode placement procedures, and device preparation to maintain the credibility of blinding. Outcome assessments and statistical analyses will be conducted by independent personnel blinded to treatment allocation. Participants will also be instructed not to discuss their intervention experiences with assessors to minimize detection bias.

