#### Group A (FES‐Integrated UPT)

2.7.1

This group will undergo treatment consisting of 30 min of FES and 30 min of UPT for 8 weeks, three times weekly. The intervention frequency of three sessions per week was selected based on previous upper‐extremity FES rehabilitation studies demonstrating functional improvements with similar training schedules [18]. Training will be provided to the physiotherapists on the FES application before the intervention begins. The XFT‐2003EA H_2_ Hand Rehab System device will be used to deliver electrical stimulations, which can be driven up to 60 mA amplitude, pulse width 250 µs, pulse frequency 40 Hz [29], to the target wrist extensor muscles according to the individual's tolerance. Participants and caregivers will be given a standard warning about the use of electrical stimulation, including watching for signs of skin burns. The electrodes of FES will be placed on the extensor carpi radialis longus and brevis, and the extensor carpi ulnaris [30]. FES will involve performing wrist extension–facilitated functional activities such as Cylindrical, Spherical, Hook, Pinch, and Thumb Adduction, focusing on power and precision. These tasks were selected because effective wrist extension is biomechanically essential for optimizing finger flexor length‐tension relationships, improving grasp stability, and facilitating functional hand use during upper‐extremity activities.

The UPT will be divided into two equal parts: (1) Spasticity management (15 min), involving passive range‐of‐motion (PROM) exercises to replicate joint movements and elongate muscles and soft tissues in segments without active movement, along with sensory stimulation techniques such as brushing and icing to modulate spasticity of the affected wrist joint during wrist flexion, extension, and rotation. (2) Active/functional upper extremity training (15 min), including hand opening/closing, gripping practice, and wrist extension/flexion tasks, with therapist‐assisted facilitation when residual movement is present, followed by relaxation techniques. All exercises will be performed at a moderate intensity (targeting 10–15 repetitions per task, adjusted to patient tolerance) to promote neuromuscular engagement and prevent fatigue [8, 9, 27]. Each session will combine FES and UPT, and each participant will receive a total of 24 treatment sessions.

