### Data Management and Monitoring

2.12

All study data will be managed in accordance with a standardized Manual of Operations and Case Report Forms (CRFs) to ensure uniformity in recruitment, assessment, data entry, and confidentiality. Staff will be trained in Good Clinical Practice, with hard copy data stored securely in locked cabinets and identifiers kept separately, while electronic data will be maintained in a secure database at the Biomedical Engineering Department, Jashore University of Science and Technology, accessible only to the principal investigator and authorized research staff. Any use of secondary data will require approval from the Data Management Committee. Monitoring will be conducted by two independent personnel not involved in the intervention, who will oversee participant enrollment, protocol adherence, adverse events, and interim analyses. Any necessary modifications to the study design or intervention will be promptly reported to the Ethical Review Board by the principal investigator.

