### Safety Measures and Adverse Effects Management

2.14

Although major side effects are unlikely, participants will be closely monitored throughout the intervention. Any adverse events (e.g., seizure, skin burn) will result in immediate discontinuation of FES and will be reported to the ethics board within 24 h. Participants will be informed of potential mild side effects such as pain, skin irritation, or discomfort, and advised to report them promptly. A history of epilepsy or seizures will be screened prior to FES application. Any serious adverse events or protocol modifications will be documented and submitted to the Institutional Review Board. Safety outcomes will be included in the final trial report to ensure comprehensive risk–benefit evaluation.

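### Section 2.11 makes emergency deviations wait for prior ethics approval and states no exception for an immediate hazard to a participant

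*Protocol article*

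**What the plan says.** Four places in the protocol article bear on this.

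- **Section 2.11, Study Procedure**, sets the general rule: "All study procedures will strictly adhere to the protocol approved by the Ethics Committee". The next sentence deals with departures from it: "Any deviations required due to emergency situations or unforeseen circumstances will be undertaken only after obtaining prior approval from the Ethics Committee". Neither sentence, nor the rest of the section, carries an exception.
- **Section 2.14, Safety Measures and Adverse Effects Management**, says that adverse events, with seizure and skin burn as its examples, "will result in immediate discontinuation of FES and will be reported to the ethics board within 24 h". Later in the same section: "Any serious adverse events or protocol modifications will be documented and submitted to the Institutional Review Board".
- **Section 2.12, Data Management and Monitoring**, says: "Any necessary modifications to the study design or intervention will be promptly reported to the Ethical Review Board by the principal investigator".
- **Section 2.7.1, Group A**, describes what is delivered: "Each session will combine FES and UPT, and each participant will receive a total of 24 treatment sessions". The usual physiotherapy (UPT) half includes passive movement and "sensory stimulation techniques such as brushing and icing" at the affected wrist. Repetitions may be adjusted to what the patient tolerates.

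**The concern.** A rule that prior approval is needed for deviations is normal. What is unusual here is that the sentence applies it expressly to emergencies, the situation in which waiting is hardest to defend. The usual arrangement is to let staff act at once when a participant faces an immediate hazard and to report afterwards. Section 2.11 does not say that, and its wording (any deviation, only after approval) leaves no room to read it in.

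What is at stake is participant protection and the position of the staff. A therapist who takes an urgent protective step that the protocol does not already prescribe must either delay it or breach the protocol. This is not an omission that a fuller document could be presumed to fill. The article states a positive rule, and a fuller text could add the exception only by contradicting it.

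**Working it through.** No arithmetic applies: the plan gives no figure on this point and none is needed. The check sets the sections against each other.

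1. **Does 2.11 contain an exception?** No. It requires strict adherence, then admits emergency or unforeseen deviations on one condition, prior approval.

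2. **Does 2.14 supply one?** In part. Stopping FES after an adverse event is a step that the protocol itself orders. Taking it is compliance, so the 2.11 condition is never triggered. For the same reason it does not license steps that are not ordered. The sentence names FES and nothing else.

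3. **Do the other sentences on changes supply one?** No. Section 2.12 has modifications to the design or intervention promptly reported. The later sentence in 2.14 has serious adverse events and protocol modifications documented and submitted. Both concern reporting, and neither mentions prior approval. They govern modifications rather than deviations, so they do not formally contradict 2.11, but they do not relax it either. Taken together, the sentence that demands approval beforehand is the one that names emergencies.

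4. **Is there an urgent step left uncovered?** Staff suspending UPT is a plausible example. A session pairs FES with UPT that handles, brushes and ices the affected wrist. After a seizure or a skin burn, a therapist might reasonably want to hold that part too. Section 2.7.1 allows repetitions to be adjusted to tolerance, but no text provides for staff to suspend UPT. The right to withdraw at any time (section 2.15) belongs to the participant and does not cover a step that staff take on their own judgement.

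5. **Result.** No section gives an immediate-hazard exception. The prescribed FES stop narrows the practical gap but does not close it.

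**The case against.** The strongest reply is that participant emergencies have their own section. Section 2.14 deals with adverse events, and its two examples are the ones most likely to arise. The 2.11 sentence follows text on assessment visits and follow-up scheduling, so it can be read as governing changes to study procedures and not individual safety. This stands in part: it limits the practical reach, and the wording of 2.11 may well be unintended. It does not remove the problem, because 2.11 speaks of any deviation and names emergencies without carving out safety.

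A second reply concerns UPT. If every session must combine FES and UPT, stopping FES may be read as ending the session, so that suspending UPT is no separate deviation. Nothing in 2.14 says that UPT carries on alone. That reading is open, so the UPT case serves as an illustration only. The point does not depend on it, since the rule would catch any urgent departure that is not already prescribed.

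A reader might infer more, and the documents do not support it:

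- **A count of sessions or a share of treatment time put at risk.** This would need an ethics approval time, which the article does not give, together with the contestable UPT reading.
- **A barrier to emergency disclosure of the allocation.** Section 2.5 says that "outcome assessors will be blinded to group allocation throughout the study period", and participants are blinded too, but the treating physiotherapists already know the allocation. Disclosure procedures are also detail that an article commonly leaves to the full protocol.
- **Randomisation of people with a seizure history.** Section 2.14 screens for it before FES and the eligibility lists do not name it. The medical screening in 2.11 is described before allocation and may already catch it. At most this is a clarification.

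**Conclusion.** The point holds in a limited form. Section 2.11 fixes a rule badly: read literally, it delays urgent protective steps other than the FES stop that 2.14 prescribes. The likeliest emergencies are already covered, and in practice staff would probably act first and report later. Severity is therefore low.

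No effect on power, sample size, bias or inference is claimed, and no numerical size can be put on the gap. The conclusion assumes that 2.11 means what it says for individual participants as well as for study procedures, and that the differently named ethics bodies in 2.11, 2.12 and 2.14 are the same one. It does not depend on how often emergencies occur or how long approval takes.

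**What to change.** Amend the deviation sentence in 2.11 along these lines: *Deviations needed to remove an immediate hazard to a participant (for example, staff suspending the physiotherapy component) are made at once and reported to the ethics board within 24 h. All other deviations require prior approval.* The 24 h limit is the one that 2.14 already uses for adverse events, so no new reporting standard is created.

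The cost is one sentence in an amendment. Section 2.16 states that recruitment has not started, so the amendment can be submitted before any participant is affected. Outcomes, sample size and analysis are unchanged.
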